# A monocenter, patient-blinded, randomized, parallel-group, non-inferiority study to compare cochlear implant receiver/stimulator device fixation techniques (COMFIT) with and without drilling in adults eligible for primary cochlear implantation

**DOI:** 10.1186/s13063-023-07568-7

**Published:** 2023-09-24

**Keywords:** Cochlear implant, Fixation technique, Bony well, Tight subperiosteal pocket, Otology, RCT, Migration, CBCT

## Abstract

**Background:**

During the cochlear implantation procedure, the receiver/stimulator (R/S) part of the implant is fixated to prevent postoperative device migration, which could have an adverse effect on the position of the electrode array in the cochlea. We aim to compare the migration rates of two fixation techniques, the bony recess versus the subperiosteal tight pocket without bony sutures.

**Methods and analysis:**

This single-blind randomized controlled trial will recruit a total of 112 primary cochlear implantation adult patients, eligible for implantation according to the current standard of practice. Randomization will be performed by an electronic data capture system Castor EDC, with participants block randomized to either bony recess or standard subperiosteal tight pocket in a 1:1 ratio, stratified by age. The primary outcome of this study is the R/S device migration rate; secondary outcomes include patient-experienced burden using the validated COMPASS questionnaire, electrode migration rate, electrode impedance values, speech perception scores, correlation between R/S migration, electrode array migration and patient complaints, assessment of complication rates, and validation of an implant position measurement method. Data will be collected at baseline, 1 week, 4 weeks, 8 weeks, 3 months, and 12 months after surgery. All data analyses will be conducted according to the intention-to-treat principle.

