#### Objectives

The primary objective of our study is to compare the migration rates of the two fixation techniques (bony recess vs. subperiosteal tight pocket) by analyzing 3D reconstructions of the R/S device, acquired by cone-beam computed tomography (CBCT) scans at baseline and at 3 and 12 months post-surgery. Secondary objectives are to investigate the difference between the two fixation techniques in patient-experienced burden using the validated COMPASS questionnaire, electrode array migration rate, and electrode impedance values. Other secondary objectives are to investigate the association of electrode impedance values with R/S device and electrode migration, and whether complaints of performance drop, vertigo, tinnitus, headache, or nonauditory stimulation are associated with electrode array migration and R/S device migration. We will also compare the complication rate of these surgical techniques, for major and minor complications. Finally, we will validate the measurement method technique with flexible tape measure for the assessment of migration of the R/S device [35].

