#### Primary outcome measure

The main outcome of this study is R/S device migration and will be calculated by analyzing 3D reconstructions of the R/S device, acquired by cone-beam CT (CBCT) scans at baseline and during follow-up and at 12 months. We consider migration either translational or rotational above 1.0 mm or 1° as clinically relevant. Any migration under these cut-offs is considered within the measurement error margin of the analysis (0.3 mm or degrees). These calculations will be carried out by using 3DMedX® (v1.2.24.1, 3D Lab Radboudumc, Nijmegen). R/S positions will be superimposed, compared, and analyzed based on the Iterative Closest Point (ICP) algorithm [36]. The 3D reconstructions of the R/S device at baseline and 12 months will be compared to calculate the primary outcome measure.

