### Sample size

This sample size calculation was based on the primary outcome, R/S migration after 12 months. Due to limited quality evidence on the migration rate for both techniques, an estimation of the migration rates cannot be based on literature; therefore, we base our assumptions on clinical expertise [34, 42, 43]. We consider a migration under 1.0 mm or 1° to be clinically irrelevant. Migration under these cut-off points is within the measurement error margin of the measurement technique of the CBCT scan analysis. A sample size of 51 per study arm reaches 80% power (*β* = 0.8) and a significance level (*α*) of 0.05 with a non-inferiority margin of 1.0 mm. Standard deviation is estimated at 2.0 mm based on the database of Maxwell et al. [43]. In order to cover for possible loss to follow-up estimated at a maximum of 10%, we will include 56 patients per study arm.

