#### Statistical analysis primary objective

The main outcome is R/S device migration calculated by analyzing 3D reconstructions of the R/S device, acquired by CBCT scans at baseline and during follow-up. Migration will be reported in millimeters and angle degrees (continuous variables) between the intervention group and the control group at baseline and 3 and 12 months after implantation. Differences between the intervention and control group will be calculated using the unpaired *t*-test or the Mann-Whitney *U* test.

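### The named primary outcome is a migration rate, but the trial is sized on mean millimetres and analysed on continuous scales, so the rate has no margin, sizing or stated test

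*Protocol article*

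**What the plan says.** All references are to the protocol article.

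- **Rate.** The Abstract (Methods and analysis) says "The primary outcome of this study is the R/S device migration rate". The aim in the Abstract (Background) is also worded as a comparison of rates. Under Objectives: "The primary objective of our study is to compare the migration rates of the two fixation techniques".
- **Cut-off.** Under Primary outcome measure: "We consider migration either translational or rotational above 1.0 mm or 1° as clinically relevant". Sample size repeats the same limits. Neither the Abstract nor Objectives states them.
- **Time point.** Under Primary outcome measure: "The 3D reconstructions of the R/S device at baseline and 12 months will be compared to calculate the primary outcome measure". Sample size agrees: "This sample size calculation was based on the primary outcome, R/S migration after 12 months".
- **Sizing.** Sample size first says that "an estimation of the migration rates cannot be based on literature; therefore, we base our assumptions on clinical expertise". It then uses a margin of 1.0 mm and "Standard deviation is estimated at 2.0 mm" to reach 51 per arm, raised to 56 for loss to follow-up. No rate appears in it.
- **Analysis.** Under Statistical analysis primary objective: "Migration will be reported in millimeters and angle degrees (continuous variables) between the intervention group and the control group". The comparison is by unpaired t-test or Mann-Whitney U test. That section mentions neither the 1.0 mm margin nor a proportion above the cut-off.

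**The concern.** A rate above a cut-off, a mean distance and a mean angle are three different quantities, and the article attaches the word primary to all three. The one it names as the outcome is not the one it sizes. The analysis section tests for a difference, although the design is non-inferiority and the only margin given is in millimetres.

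What is at stake is the conclusion. The Discussion says that the safety of the pocket technique is not yet proven with certainty, so readers will want to know how many devices move by a relevant amount. A mean can stay within 1.0 mm of control while the share of patients above 1.0 mm differs considerably. If the trial passes on the mean and is then reported in the words of its stated objective, it will claim something about migration rates that it never tested.

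**Working it through.** **1. Which quantity was sized?** Inputs from Sample size: margin 1.0 mm, SD 2.0 mm, 80% power, alpha 0.05 (sidedness not stated). Assume no true difference.

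- Normal approximation: n per arm = 2 × SD² × (z₀.₉₅ + z₀.₈₀)² / margin² = 2 × 4 × (1.645 + 0.842)² / 1 = 49.5, so 50.
- Exact noncentral t: 50 per arm gives 79.9% power and 51 gives 80.6%. The stated 51 is reproduced as a one-sided 5% comparison of two means. At one-sided 2.5% the exact figure would be 64.

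No event rate and no margin on a rate enter this calculation.

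**2. What each quantity has in the article**

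| Quantity | Named as primary | Margin | Sizing | Stated analysis |
|---|---|---|---|---|
| Rate above 1.0 mm or 1° | Abstract, Objectives (as a rate, without the cut-off) | none | none | none |
| Migration in mm | Primary outcome measure, Sample size | 1.0 mm | 51 per arm | t-test or Mann-Whitney for a difference |
| Migration in degrees | Primary outcome measure, analysis section | none | none | t-test or Mann-Whitney for a difference |

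A non-significant difference test does not establish non-inferiority, and a Mann-Whitney test does not use a margin in millimetres directly. The margin has to be tied to the test in words.

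**3. Can the mean pass while the rate is much worse?** Assume that the analysis requires the upper one-sided 95% bound for the mean difference (unequal variances) to lie below 1.0 mm. The distributions below are also assumptions, because the article gives none.

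- Control: 0.4 mm with SD 0.3 mm. Pocket: the same, except that 30% of devices move a further 2 mm.
- Share above 1.0 mm: control P(Z > (1.0 − 0.4)/0.3) = P(Z > 2) = 2.3%. Pocket 0.30 × 1.00 + 0.70 × 0.023 = 31.6%.
- Mean difference: 0.30 × 2 = 0.60 mm.
- SDs: control 0.30 mm. Pocket √(0.3² + 2² × 0.3 × 0.7) = √0.93 = 0.96 mm.
- Standard error with 51 per arm: √((0.93 + 0.09)/51) = 0.141 mm. The distance to the margin is (1.0 − 0.60)/0.141 = 2.83 standard errors.
- Over 20,000 simulated trials, non-inferiority is declared in 86% to 87%, depending on how negative noise values are handled.

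**4. How far this depends on the SD.** With normal data, SD 2.0 mm in both arms and the same 0.60 mm difference, the standard error is 2 × √(2/51) = 0.396 mm and the pass probability is about 26%. Less favourable shapes with SDs near 2.0 mm can still separate the two measures:

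- SDs 1.9 and 1.7 mm, means 1.0 and 1.1 mm, shares above 1 mm of 10% (control) and 45% (pocket): passes in 81% of trials.
- SDs 1.9 and 2.0 mm, means 1.0 and 1.3 mm, shares of 10% and 38%: passes in 65%.

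Both need the few control migrations to be several millimetres each.

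**5. What a rate endpoint would need.** At an assumed true rate of 10% in both arms, one-sided 5% and 80% power, a 10-point margin needs about 112 per arm and a 15-point margin about 50. With 51 per arm, the smallest margin with 80% power is (1.645 + 0.842) × √(2 × 0.1 × 0.9/51) = 0.148, about 15 points.

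**The case against.** The best defence is that *rate* is loose wording for amount of migration. The Primary outcome measure section names the outcome simply as migration, the sizing is in millimetres and reproduces, and the analysis variables are expressly continuous. On that reading only the Abstract and Objectives need editing. This is fair as to the intention, and it is why the fix keeps the sizing. It does not remove the contradiction: the aim, the named outcome and the primary objective all say rate, and a cut-off that would define such a rate is given.

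Four stronger readings are tempting and not supported:

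- *That 3 and 12 months compete as primary time points.* They do not. The outcome section and the sizing both fix 12 months.
- *That the objective itself carries the cut-off.* It does not. The limits stand in the outcome and sample size sections only.
- *That the planned test would probably pass a much worse technique.* The analysis section states no non-inferiority test, so the rule simulated above is borrowed from the sample size section. The 87% also rests on SDs well below the protocol's 2.0 mm.
- *That using two scales inflates error or costs power by a known amount.* Any such figure needs a margin and an SD for degrees, and the article gives neither. A rule for combining scales may also stand in an analysis plan that is not shown.

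It can also be said that keeping the mean as primary does not stop the mean and the rate from diverging. That stands. The fix makes the claim match the test and puts the rate in view. It does not turn the trial into a test of the rate.

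**Conclusion.** The point holds as a contradiction within the article. The named primary outcome, a migration rate, has no margin, no sizing and no stated analysis. The quantity that was sized, mean millimetres, is not what the Abstract and the primary objective name. Degrees have no margin, and the 1.0 mm margin is not connected to the planned test. A conclusion about non-inferior migration rates would not follow from the plan as written.

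The possible gap between mean and rate is large (32% against 2% above 1.0 mm, passing in about 87% of trials), but this rests on an assumed decision rule and assumed distributions with SDs of about 0.3 and 1.0 mm. It shows that a pass on the mean cannot stand in for the rate. It does not show that such a result is likely. The sizing is sound for what it sizes, taken as one-sided 5%.

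**What to change.** - Name one primary endpoint that matches the sizing: mean translation in millimetres from the scan within 48 hours of surgery to 12 months.
- In Statistical analysis primary objective, state that non-inferiority is judged by the upper confidence bound for the difference in means against the 1.0 mm margin.
- Replace *migration rate(s)* in the Abstract (aim and primary outcome) and in the primary objective.
- State that rotation is secondary and carries no non-inferiority claim.
- Report the proportion above 1.0 mm or 1 degree in each arm, with a risk difference and confidence interval, as the first secondary outcome.
- State that non-inferiority of the migration rate will not be claimed from the mean.

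The cost is wording and one extra table row, with no added patients. The downside is a narrower headline claim. If the rate is what the sponsor wants to conclude on, it needs its own margin and sample size, for example about 112 per arm at an assumed 10% rate and a 10-point margin.

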**Discussion:**

Cochlear implantation by means of creating a tight subperiosteal pocket without drilling a bony seat is a minimally invasive fixation technique with many advantages. However, the safety of this technique has not yet been proven with certainty. This is the first randomized controlled trial that directly compares the minimally invasive technique with the conventional method of drilling a bony seat.

**Trial registration:**

Netherlands Trial Register NL9698. Registered on 31 August 2021.

**Supplementary Information:**

The online version contains supplementary material available at 10.1186/s13063-023-07568-7.

## Background

### Background and rationale

Cochlear implants (CIs) provide hearing through direct electrical stimulation of the auditory nerve in patients with sensorineural hearing loss and have become standard care for adult and pediatric patients with severe to profound bilateral hearing loss. Cochlear implantation surgery requires careful planning and execution. The correct electrode array positioning in the cochlea is crucial for optimal functionality of the device. This array is connected to the body of the implant, known as the receiver/stimulator (R/S) device. During cochlear implantation, the R/S device is placed and fixated on the skull. It should be placed close to the pinna, without possible interference of the microphone in the behind-the-ear device laying (partially) on top of the R/S device.

The standard fixation technique of the R/S device, which is recommended by the surgeon’s guide that is supplied with the respective implants, consists of drilling out a part of the bony cortex of the skull (a bony recess), as well as non-absorbable suture retaining holes [1]. The bony recess technique lowers the profile of the R/S device in relation to the skull surface and holds it in place with non-absorbable sutures to the bone. Although rare, complications that are due to drilling of the bony recess can have serious consequences. Depending on the extent of drilling and the cortex thickness of the patient, the dura mater is sometimes exposed [2, 3]. Several studies report on dural tears with subsequent cerebrospinal fluid leakage as a direct result of extensive cortical drilling [4–6]. Other complications that have been reported (but occur very rarely) and associated with this technique are late-onset hematomas, epi-/subdural hematoma, tentorial herniation, and cerebral infarction, as well as meningitis [5, 7–11]. To avoid such risks, in recent years ENT surgeons have adopted less invasive techniques [1–3, 10, 12–20]. Additionally, later CI models have a lower profile and a flatter bottom. However, the lowering of the profile is a trade-off for a larger footprint which results in a larger bony recess thus a larger area of the skull is drilled out.

Complications that can occur as a result of failed fixation of the R/S is a shift/migration of the internal components of the implant: the R/S device itself and the electrode array [16, 21]. Migration of the R/S device can lead to pain/headache, behind-the-ear device problems, hematoma, device failure, and in some cases necessitating revision surgery [19, 22–26]. It can also have an effect on the position of the electrode array in the cochlea. Electrode migration or extrusion is one of the most common indications for revision surgery [23–25]. This complication can cause poor performance, pain, vertigo, tinnitus, and facial nerve stimulation, but can also present without complaints [27]. Increase in impedance values has also been described as a result of electrode array migration [28]. The rate of reported electrode migration varies in the literature and seems to occur more than previously thought [27, 29].

A minimally invasive technique that does not require drilling out a bony recess, known as the subperiosteal tight pocket technique, was first described by Balkany et al. in 2009 [10]. This technique uses the anatomical boundaries of the pericranium to create a tight subperiosteal pocket in which the R/S device is inserted. Apart from the advantage of not having to drill out a bony recess, thus eliminating the risk of complications associated with the bony recess, the subperiosteal tight pocket technique also has the advantage of a smaller incision and shorter operating time [16]. Creating the subperiosteal pocket might also require less manipulation and straining of the temporalis muscle (compared to the mentioned bony recess technique), thereby reducing postoperative pain or tissue-related complaints even more.

Since the publication of the study by Balkany et al. in 2009, many ENT specialists are applying the tight subperiosteal technique [1, 2, 12–14, 16–18, 20, 30–33]. However, since the R/S device is not fixated in a bony recess or by sutures, migration of the device is a point of concern due to the complications that can occur. To evaluate the difference in migration rates between the fixation technique currently used in our center (the bony recess technique), and the intervention technique (subperiosteal tight pocket technique), we conducted a literature review [34]. The results were inconclusive due to a lack of high-quality studies from a methodological point of view. Thus, there is no quality evidence to support the superiority of either technique. Therefore, in the COMFIT trial, we aim to compare the subperiosteal tight pocket technique with the bony recess technique, for fixation of the R/S device of the cochlear implant.

#### Objectives

The primary objective of our study is to compare the migration rates of the two fixation techniques (bony recess vs. subperiosteal tight pocket) by analyzing 3D reconstructions of the R/S device, acquired by cone-beam computed tomography (CBCT) scans at baseline and at 3 and 12 months post-surgery. Secondary objectives are to investigate the difference between the two fixation techniques in patient-experienced burden using the validated COMPASS questionnaire, electrode array migration rate, and electrode impedance values. Other secondary objectives are to investigate the association of electrode impedance values with R/S device and electrode migration, and whether complaints of performance drop, vertigo, tinnitus, headache, or nonauditory stimulation are associated with electrode array migration and R/S device migration. We will also compare the complication rate of these surgical techniques, for major and minor complications. Finally, we will validate the measurement method technique with flexible tape measure for the assessment of migration of the R/S device [35].

#### Trial design

This is a single-blind, non-inferiority randomized controlled trial, with two study arms (Fig. 1). Patients will be randomly allocated into equally sized groups: group A and group B (allocation ratio 1:1). Patients in group A will be operated with the bony recess technique, and patients in group B will be operated with the subperiosteal tight pocket technique. Inclusion in the study will have no consequence for the model or brand chosen by the patient, as is currently standard practice.

**Fig. 1 Fig1:**
[figure not shown]
Flowchart of the study. CBCT: cone-beam CT scan; COMPASS questionnaire: patient-reported outcome measure on cochlear implant awareness. Patients will be randomized into two groups according to variable, weighted block randomization module subgroups with stratification for age (18–50 years, and > 50 years)

## Methods: participants, interventions, and outcomes

### Study setting

This is a monocenter study performed in a tertiary referral clinic in the Netherlands, the University Medical Center (UMC) Utrecht.

### Eligibility criteria

The study population consists of adult patients (> 18 years old) that are approved for cochlear implantation according to standard care criteria. Patients will initially undergo a series of diagnostic tests to assess eligibility for cochlear implantation. These are as follows: a CT scan, a pure tone audiogram/speech test, psychological evaluation, and a consultation by the audiologist and ENT specialist. The Cochlear Implant Team of the UMC Utrecht will assess the work-up results and assess eligibility for cochlear implantation, according to the current clinically applied criteria.

All cochlear implant models will be included in this study. The choice for the cochlear implant model lies with the patient and the CI team of the UMC Utrecht and will not be affected by taking part in this trial. In order to be eligible to participate in this study, a participant must have provided written informed consent authorization before participating in the study. They also must have Dutch written language proficiency and be physically able to undergo a CBCT scan.

A potential participant who is a revision or reimplantation candidate, is unable to understand or sign informed consent, or is pregnant during the trial will be excluded from participation in this study.

### Interventions: description

The standard surgical procedures for cochlear implantation will be followed. A retroauricular S-shaped incision will be made to expose the mastoid. The electrode array will be inserted via a posterior tympanotomy and round window implantation by soft-surgery techniques. The R/S device will be fixated according to the group the patient is allocated to. The bony recess technique will be used in group A; a bony recess will be drilled at an angle of 30 to 60° relative from the Frankfurt Horizontal plane. The provided silicone dummy will be used to ensure the depth and dimensions of the recess are sufficient. No tie-down sutures will be used. Patients allocated to group B will be operated using the subperiosteal tight pocket technique as described by Balkany et al. [10].

